#### Primary outcome

To indicate group differences in walking time per day (average values of the first, third, and sixth week of the home period, e.g., T2–T4), an ANCOVA will be performed using the pre-intervention values (T0) as covariates.

A secondary analysis will be performed on walking time per day for the combined Myosuit home use periods (average values of the first, third, and sixth week of the home period (T2-T4) versus pre-intervention values (T0) for the intervention group and average values of the first, third, and sixth week of the home period (T7-T9) versus pre-intervention values (T4) for the control group) to investigate whether specific personal characteristics are related to improvement resulting from Myosuit use. This analysis involves a regression model with the difference in minutes walking time per day as dependent variable and personal characteristics (such as lesion level, ASIA score, and age) as independent variables. No other analyses are preplanned.

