### Allocation

Participants will be randomly allocated to either the intervention group (receiving the Myosuit program) or the control group (initially receiving the conventional program) using a block randomization method. After completion of the conventional program, the control group will as yet be enrolled in the Myosuit program (see Fig. 1). Randomization will be stratified based on preferred walking speed as assessed by the 10-Meter Walk Test (2 categories: < 0.6 m/s; ≥ 0.6 m/s). Group allocation will be done using a 1:1 ratio and in blocks with variable block sizes. Randomization will be performed by the primary researcher (LV), who is aware of the method of the group allocation. CastorEDC, a data management system for academic studies (www.castoredc.com), is used for the randomization.

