### Sample size

An improvement of 500 steps per day is considered clinically relevant, corresponding to a 33% improvement of a baseline with 1500 steps per day [48]. Based on a stride time of 1.07 s, 500 steps per day corresponds to an increase of 4.5 min walking time per day [49]. For each group, a sample size of *N* = 14 is needed to demonstrate a difference in improvement of 500 steps per day between groups (SD = 400, *α* = 0.05, *β* = 0.10) [48]. Three patients will be added to each group (*N* = 17) allowing an 18% attrition rate; therefore, we aim to include a total of 34 participants. Sample size calculation is based on conducting analysis of variance (ANOVA) due to the absence of data for calculating a correlation that would be required for sample size calculation based on analysis of covariance (ANCOVA). Generally, statistical power of ANCOVA is higher than that of ANOVA.

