#### Secondary outcomes

Group differences in gait capacity (PWS, MWS, 6MWT, SCI-FAP) after the intervention (T5) and spatiotemporal gait characteristics of daily life gait performance (walking speed, step length, maximum gait bout length, and double support phase duration) averaged over the first and sixth week of the home period (T2 and T4) will be tested with an ANCOVA using the pre-intervention values (T0) as covariates. Costs collected during the study will be specific Myosuit costs and training costs per patient for the intervention group and trainings costs per patient for the control group. Total QALYs will be assessed by the area under the curve. Short-term impact on both costs and QALYs will be analyzed by calculating the between-group differences in average costs per patient and average QALYs between T5 (after the intervention) and T0 (pre-intervention values). Cost differences will be expressed per costing category (average Myosuit costs and training costs per patient) to ensure insight is provided with regard to the impact on individual costing parameters. The results of the D-QUEST, SUS, and GDSSeS will be evaluated by descriptive analyses (mean and standard deviation).

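### Randomisation is stratified by preferred walking speed but the stated ANCOVAs omit the stratum; adding it would cost almost nothing and may recover a little precision

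*Protocol article*

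**What the plan says.** Under Allocation: "Randomization will be stratified based on preferred walking speed as assessed by the 10-Meter Walk Test", with two categories split at 0.6 m/s. The same section adds: "Group allocation will be done using a 1:1 ratio and in blocks with variable block sizes".

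Under Statistical methods, Primary outcome, walking time per day averaged over T2–T4 is compared between groups, and "an ANCOVA will be performed using the pre-intervention values (T0) as covariates". In context this means the T0 value of the outcome. After describing one further regression on personal characteristics, the section closes with "No other analyses are preplanned".

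Under Statistical methods, Secondary outcomes, gait capacity at T5 (preferred speed, maximum speed, 6MWT, SCI-FAP) and the spatiotemporal gait characteristics "will be tested with an ANCOVA using the pre-intervention values (T0) as covariates".

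The walking-speed stratum is not named in any of these models.

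**The concern.** Stratified blocks keep the two arms nearly balanced on walking speed, so differences in speed contribute little to chance variation in the treatment estimate. Suppose the stratum explains part of the outcome that the T0 value does not. A model without the stratum then leaves that part in the residual variance, and the reported standard error describes a less precise design than the one used. Confidence intervals come out too wide, the true type I error falls below 5%, and some power is given up.

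At stake is a modest amount of precision in a small trial. When the term is added also matters. The Blinding section justifies an unblinded analysis on the ground that the analyses were fixed in advance. A stratum term brought in after the data are seen would therefore be a discretionary choice.

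**Working it through.** **Inputs from the protocol article.**
- Two strata, 1:1 allocation, variable blocks (Allocation).
- Planned difference and SD: "a difference in improvement of 500 steps per day between groups (SD = 400"; α = 0.05, β = 0.10 (Sample size). Sidedness is not stated; two-sided is assumed.
- Attrition: "Three patients will be added to each group (*N* = 17) allowing an 18% attrition rate", so 2 × 14 = 28 completers out of 34.

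**Inputs that are assumptions.**
- Partial R² of the stratum given the T0 outcome value: 0 to 0.30. The documents give no figure.
- Correlation between walking speed and T0 walking time: 0.5.
- Two equal strata, and blocks of 2 or 4.
- SD given T0, before the stratum is added, held at 400.

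**Step 1: the plan's own figure.** n per group = 2 × [400 × (1.960 + 1.282)/500]² = 13.45, rounded up to 14. The stated figure reproduces. Power at 14 per group is 91.1% by the normal approximation and 88.9% by the exact t-test, which is why the simulated powers below start just under 90%.

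**Step 2: expected effect of adding the stratum.** Without it, SE ≈ 400 × √(2/14) = 151. With it, SE is multiplied by about √(1 − R²). The reduction is 1 − √0.90 = 5% at R² = 0.10, 1 − √0.80 = 11% at 0.20 and 1 − √0.70 = 16% at 0.30.

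**Step 3: simulation**, 14 per group, difference 500, 10,000 trials per setting. Each pair is T0 only, then T0 plus stratum.

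| Partial R² | Mean model SE | Power (%) | Type I error (%) |
|---|---|---|---|
| 0 | 152 / 153 | 87.3 / 87.0 | 5.1 / 5.1 |
| 0.05 | 153 / 149 | 88.0 / 88.7 | 4.5 / 5.0 |
| 0.10 | 153 / 146 | 88.3 / 90.1 | 4.6 / 5.5 |
| 0.20 | 153 / 137 | 89.2 / 93.3 | 3.7 / 5.2 |
| 0.30 | 154 / 129 | 89.7 / 95.8 | 2.7 / 4.9 |

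The falls in SE match Step 2. A separate run at partial R² of 0, 0.10, 0.20 and 0.30 agreed within simulation error: power 86% for both models, then 88 to 91%, 89 to 93% and 89 to 96%, with type I error of the planned model about 5, 4, 3.6 and 2.8%.

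**Step 4: how far the planned model overstates its own error.** Its estimate actually varied with an SD of 147.9, 141.6 and 136.4 at R² of 0.10, 0.20 and 0.30, against mean model SEs of 153.0, 152.8 and 153.6. The ratios are 153.0/147.9 = 1.03, 152.8/141.6 = 1.08 and 153.6/136.4 = 1.13.

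**Step 5: all 34 analysed.** The gains shrink to about 0, 1, 2 and 3 points at R² of 0, 0.10, 0.20 and 0.30, because power is already about 94% without the stratum.

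**Step 6: preferred walking speed as outcome.** Its T0 covariate is the continuous form of the stratum. Adding the stratum moves SE from 151 to 153 and power from 87.9% to 86.5%, so nothing is gained.

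**The case against.** A reader might infer that standard errors are too large and power is lost in every planned ANCOVA. The documents do not support that.

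- **The loss is conditional.** It needs the stratum to predict the outcome beyond the T0 value. The Introduction links reduced gait capacity to limited walking at home and in the community, but that does not show what remains once T0 walking time is in the model. The Sample size section says that not even the correlation needed for an ANCOVA calculation was available. At zero association the added term costs about 0.3 points of power. This stands.
- **Not every outcome is affected.** The preferred-speed model already carries the information. T0 maximum speed, T0 6MWT distance and T0 daily-life walking speed are themselves close to walking speed, so a two-level cut probably adds little there; that is an inference. This stands.
- **The planned power is not undercut.** The sample size rests on ANOVA and takes no credit for any covariate. The T0-adjusted ANCOVA is valid, and any error is on the cautious side. This stands.
- **An article condenses, and a separate analysis plan may list the stratum.** This stands in part. Excluding further analyses does not settle every term of the named ANCOVA. Still, the article does state the covariates for the primary and secondary models, and the stratification factor is not among them.

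**Conclusion.** The stated models do not match the stratified design, and the direction of any error is known: standard error too large, test conservative. The size depends on an association that the documents do not give. With 28 completers and the planned 1.25 SD effect, adding the stratum is worth about 0, 2, 4 and 6 points of power at partial R² of 0, 0.10, 0.20 and 0.30; with 34 analysed, about 0, 1, 2 and 3. Type I error of the planned model falls from 5% to just under 3% across that range.

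These figures rest on the assumed 0.5 correlation, equal strata and small blocks. They also treat the 28 completers as balanced within strata, which dropout would loosen.

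It would be wrong to read this as bias, inflated type I error or an underpowered trial. It is a minor point of efficiency and calibration, and a free improvement.

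**What to change.** Before the data are analysed, specify the primary model as an ANCOVA of mean T2–T4 walking time on arm, T0 walking time and walking-speed stratum (or T0 preferred walking speed as a continuous covariate). Add the same term to the secondary ANCOVAs except the one for preferred walking speed. Expect little gain for maximum speed, 6MWT and daily-life walking speed. If a separate analysis plan already contains the term, bring the published description into line with it.

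The cost is one residual degree of freedom per model (with 28 analysed, 25 becomes 24). No new data are needed, because the stratum had to be known at randomisation. The sample size does not change.

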#### Secondary outcomes

Group differences in gait capacity (PWS, MWS, 6MWT, SCI-FAP) after the intervention (T5) and spatiotemporal gait characteristics of daily life gait performance (walking speed, step length, maximum gait bout length, and double support phase duration) averaged over the first and sixth week of the home period (T2 and T4) will be tested with an ANCOVA using the pre-intervention values (T0) as covariates. Costs collected during the study will be specific Myosuit costs and training costs per patient for the intervention group and trainings costs per patient for the control group. Total QALYs will be assessed by the area under the curve. Short-term impact on both costs and QALYs will be analyzed by calculating the between-group differences in average costs per patient and average QALYs between T5 (after the intervention) and T0 (pre-intervention values). Cost differences will be expressed per costing category (average Myosuit costs and training costs per patient) to ensure insight is provided with regard to the impact on individual costing parameters. The results of the D-QUEST, SUS, and GDSSeS will be evaluated by descriptive analyses (mean and standard deviation).

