**Fig. 1 Fig1:**
[figure not shown]
Schematic overview of the study design

Participants in the intervention group receive the Myosuit program which consists of five gait training sessions (in 3 weeks) with the Myosuit at the Sint Maartenskliniek. Thereafter, questionnaires regarding the usability will be delivered (T1). In addition, participants will perform a test to receive a certificate for using the Myosuit themselves at home. A 6-week home period follows, during which participants have access to the Myosuit. Measurements of daily life gait performance will be conducted during the first, third, and sixth week of the home period (T2, T3, T4). After the 6-week home period, measurements of gait capacity, usability, and quality of life will be taken at the Sint Maartenskliniek (T5).

Participants in the control group will receive four gait training sessions (in 2 weeks) at the Sint Maartenskliniek, followed by a 6-week home. Measurements of daily life gait performance will be conducted during the first, third, and sixth week of the home period (T2, T3, T4). After the 6-week home period, measurements of gait capacity and quality of life will be taken at the Sint Maartenskliniek (T5). Thereafter, the control group will as yet be enrolled in the Myosuit program which will be identical to the Myosuit program of the intervention group. Usability questionnaires will be delivered at T6 and daily life gait performance will be assessed during the first, third, and sixth week of the home period (T7, T8, T9). Measurements of gait capacity, usability, and quality of life will be taken at T10.

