##### Quality-adjusted life years (QALY) gain and costs

The European Quality of Life Five Dimension (EQ-5D-5L) will be used to calculate gained QALYs [42, 43]. The EQ-5D-5L is a questionnaire that measures a patient’s health state across five dimensions: mobility, self-care, usual activities, pain/discomfort, and anxiety/depression. Scores on each dimension range from 1 to 5, with a higher score indicating a better health state. The EQ-5D-5L will be delivered at T0 (baseline), T5, and T10 (after the intervention). Measurements at T0 (baseline) and T5 (after the intervention) will be analyzed. In addition, actual costs associated with the intervention (Myosuit program) will be calculated, including costs related to providing physical therapy, the Myosuit purchase costs, and the Myosuit maintenance costs. Costs associated with the conventional program are costs related to providing physical therapy. The costs for physical therapy will be calculated based on the average wages of current rehabilitation physiotherapy professionals in The Netherlands indicated by the Dutch Health Care Institute.

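### QALYs are totalled from T0 to T5 with no common horizon, although the schedule makes that window nominally 9 weeks in the Myosuit arm and 8 weeks in the control arm

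*Protocol article*

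**What the plan says.** The statistical methods for secondary outcomes in the protocol article state that "Total QALYs will be assessed by the area under the curve". The short-term impact is then obtained by "calculating the between-group differences in average costs per patient and average QALYs between T5 (after the intervention) and T0".

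The section on QALY gain and costs says that the EQ-5D-5L "will be used to calculate gained QALYs". It names the two time points used: "Measurements at T0 (baseline) and T5 (after the intervention) will be analyzed".

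The Procedure section fixes the calendar. T0 is completed before randomization. The Myosuit arm then has "five gait training sessions (in 3 weeks) with the Myosuit", a 6-week home period, and T5. The control arm has "four gait training sessions (in 2 weeks) at the Sint Maartenskliniek, followed by a 6-week home" period, and then T5. The article gives no common QALY horizon, no division by follow-up time, and no T5 date counted in weeks from T0.

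**The concern.** A total area under the utility curve is utility multiplied by time, so it grows with the length of the window. If one arm is followed for longer between T0 and T5, it accumulates more QALYs whether or not its participants feel better. Here the longer window belongs to the Myosuit arm, so the schedule alone pushes the contrast in favour of the intervention. The push is systematic: recruiting more participants would not shrink it.

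At stake is the interpretation of the last stated objective, the short-term impact on costs and effects. A difference in average QALYs could be reported as a benefit of the device when part or all of it comes from the visit calendar.

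A lesser point concerns baseline. With only T0 and T5 in the curve, half of each participant's total is weight on the T0 utility. The planned contrast is an unadjusted difference in averages, whereas the gait capacity and spatiotemporal outcomes are analysed by ANCOVA on their T0 values.

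**Working it through.** The article reports no QALY figure, so there is none to reproduce. The check derives the windows and then applies the stated method.

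**Inputs from the article**
- Start: T0, before randomization in both arms (Procedure).
- Myosuit arm: 3 weeks of training, then 6 weeks at home, then T5 (Procedure).
- Control arm: 2 weeks of training, then 6 weeks at home, then T5 (Procedure).
- Utilities used: T0 and T5 only (section on QALY gain and costs).

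**Input assumed**
- Mean utility u between 0.5 and 0.8, because the article gives none.

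**Step 1: nominal windows**
- Myosuit: 3 + 6 = 9 weeks.
- Control: 2 + 6 = 8 weeks.

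**Step 2: total QALYs with two measurements**
- With 365.25/7 = 52.18 weeks per year, QALY = (U_T0 + U_T5)/2 × weeks/52.18.

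**Step 3: no effect, same constant utility u in both arms**
- Ratio of totals: 9/8 = 1.125, so the Myosuit arm scores 12.5% more.
- Difference: u × (9 − 8)/52.18 = u/52.18.

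| Assumed u | Myosuit, 9 weeks | Control, 8 weeks | Difference |
|---|---|---|---|
| 0.5 | 0.0862 | 0.0767 | 0.0096 |
| 0.6 | 0.1035 | 0.0920 | 0.0115 |
| 0.7 | 0.1207 | 0.1073 | 0.0134 |
| 0.8 | 0.1380 | 0.1227 | 0.0153 |

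**Step 4: the same amount expressed as a utility change**
- A linear change d by T5 in the Myosuit arm is worth d/2 × 9/52.18. Setting this equal to u/52.18 gives d = 2u/9.
- At u = 0.5, d = 0.11. At u = 0.8, d = 0.18.
- A fall of that size in the Myosuit arm alone would leave the two totals equal.

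**Step 5: the other reading, area above each participant's own baseline**
- The difference for an equal linear gain d in both arms is d/2 × 1/52.18.
- At d = 0 it is 0. At an assumed d = 0.05 it is about 0.0005 QALY.

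**Step 6: a common horizon**
- With H weeks in both arms and the same constant utility, the difference is u × (H − H)/52.18 = 0.

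**The case against.** The best counter-argument is that the article does not settle which quantity is meant. The section on QALY gain and costs speaks of QALYs gained, and the statistical section's reference to T5 and T0 resembles the change-from-baseline wording used for other outcomes. On that reading Step 5 applies and the artefact almost disappears. This stands as a real ambiguity. However, the statistical section, which governs the analysis, refers to total QALYs and describes no subtraction of baseline, so the literal reading carries the extra week.

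Second, 9 and 8 weeks are derived, not stated. T0 includes a 7-day activity recording and cancelled sessions are rescheduled, so actual intervals will vary. That also stands, and the figures are nominal. Nothing in the text, though, removes the planned one-week difference.

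Third, an article may leave detail to a fuller plan. Here, however, the article itself fixes the metric, the time points and the contrast, and together with the schedule these give the unequal comparison.

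Three stronger inferences are tempting and are not supported:
- A reader might conclude that the artefact exceeds any plausible benefit. The article gives neither utilities nor an expected utility gain, so no such ratio can be drawn from it.
- A reader might say that QALYs are the only T0/T5 outcome left unadjusted. The self-efficacy scale is also measured at T0 and T5 and is evaluated only descriptively.
- A reader might treat chance baseline imbalance as adding to the artefact. Under randomization it has no fixed direction and could equally offset it. It is a reason to adjust, not a second bias.

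**Conclusion.** The point holds in a limited form. By the article's own schedule and its literal analysis wording, the QALY contrast gives the Myosuit arm about one extra week of utility with no treatment effect. This is 12.5% at equal constant utility, or 0.010 to 0.015 QALY for assumed mean utilities of 0.5 to 0.8. The direction is the same for any positive mean utility.

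The conclusion rests on three things: nominal windows of 9 and 8 weeks, total rather than baseline-subtracted QALYs, and two-point area under the curve. If baseline-subtracted QALYs are intended, the artefact is near zero and the remaining problem is wording.

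A reader might infer that the trial's main result is compromised. It is not: the primary outcome is mean walking time per day, which does not accumulate over the T0 to T5 interval. The economic contrast is the last-listed objective and is planned only as differences in averages. The text should be corrected before the economic analysis is run, but this is not a fault that threatens the trial.

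**What to change.** Amend the QALY sentences in the statistical methods for secondary outcomes:

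1. State that QALYs are computed over one common horizon in both arms. Either interpolate each participant's utility to week 8 and integrate to that point, or take mean utility over T0 and T5 and multiply by a fixed duration. Choose one in advance; both give zero when utility is constant and equal.
2. Estimate the between-arm difference by regression on arm with T0 utility as covariate. This adjusts for chance baseline imbalance and matches the ANCOVA planned for the gait outcomes. It does not replace item 1, because baseline adjustment alone leaves the extra week in a total.
3. Say in both places whether QALYs are total or gained over baseline, so that the outcome section and the analysis section describe the same quantity.

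The cost is a few sentences of analysis wording. No new assessments are needed: the existing T0 and T5 questionnaires suffice, with visit dates if interpolation is chosen. At publication 23 of the 34 planned participants had been included and recruitment was still open, so the change can be made before the analysis.

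### Total QALYs from T0 to T5 are compared over a window one week longer in the Myosuit arm; as written, this favours the Myosuit when it has no effect

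*Protocol article*

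**What the plan says.** All references are to the protocol article.

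- **Estimand (Statistical methods, Secondary outcomes).** "Total QALYs will be assessed by the area under the curve". The comparison is made by "calculating the between-group differences in average costs per patient and average QALYs between T5 (after the intervention) and T0 (pre-intervention values").
- **Myosuit timeline (Procedure, text under Fig. 1).** The programme has "five gait training sessions (in 3 weeks) with the Myosuit at the Sint Maartenskliniek", then a 6-week home period, then T5.
- **Control timeline (same place).** The control group receives "four gait training sessions (in 2 weeks) at the Sint Maartenskliniek, followed by a 6-week home" period, then T5.
- **EQ-5D-5L (Quality-adjusted life years (QALY) gain and costs; Table 1).** It is administered at T0, T5 and T10, and the T0 and T5 measurements are analysed. This section speaks of *gained* QALYs and gives no formula.

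No section sets a common time horizon for QALYs, rescales for follow-up time or adjusts QALYs for T0 utility. By contrast, gait capacity and the spatiotemporal measures are analysed by ANCOVA with the T0 value as covariate.

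**The concern.** A total area under the utility curve grows with the length of the window. Here the window depends on the arm: the Myosuit programme has one more week of training before the home period starts. Two groups with identical, unchanging quality of life would therefore end with different total QALYs, and the difference would always favour the Myosuit.

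This is not a chance imbalance that randomisation evens out, and a larger sample would only estimate it more precisely. Entering T0 utility as a covariate does not remove it either, because the arm term still carries mean utility times one week.

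QALYs are the effect side of the stated objective on short-term costs and effects, so that comparison could show a benefit that comes from the calendar alone.

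**Working it through.** The article states no QALY figure to reproduce, so the check follows its rule with its own phase lengths.

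**Inputs**
- Training: 3 weeks (Myosuit), 2 weeks (control). Home period: 6 weeks in both. Source: Procedure.
- Utility measured at T0 and T5 only, so the area is a trapezoid.
- Mean utility *u*: not given. Assumed equal and constant in both arms, at 0.6, 0.7 or 0.8.
- Shared time between T0 and the start of training: not given. T0 includes 7 days of activity monitoring (Assessments, Primary outcome), and randomisation follows the T0 assessments (Procedure). Assumed 0, 1 or 2 weeks, the same in both arms.

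**Step 1. Windows.** Myosuit 3 + 6 = 9 weeks; control 2 + 6 = 8 weeks. Shared lead-in weeks add equally to both.

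**Step 2. Relative excess under no effect.**
- No lead-in: 9/8 − 1 = 12.5%
- One week: 10/9 − 1 = 11.1%
- Two weeks: 11/10 − 1 = 10.0%

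**Step 3. Absolute excess under no effect.** It is *u* × 1/52, whatever the lead-in:
- *u* = 0.6: 0.0115 QALYs
- *u* = 0.7: 0.0135 (without lead-in, 0.7 × 9/52 = 0.1212 against 0.7 × 8/52 = 0.1077)
- *u* = 0.8: 0.0154

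**Step 4. Scale.** Take a true utility gain of 0.05 by T5, linear from T0 (an assumption). Over a Myosuit window of *W* weeks it is worth 0.5 × 0.05 × *W*/52:
- *W* = 9: 0.0043 QALYs
- *W* = 10: 0.0048

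The ratio of artefact to true gain is (*u*/52) / (0.025 × *W*/52) = *u*/(0.025 × *W*):
- *W* = 9: 0.6/0.225 = 2.7 to 0.8/0.225 = 3.6
- *W* = 10: 0.6/0.25 = 2.4 to 0.8/0.25 = 3.2

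With two lead-in weeks (*W* = 11) the lower end falls a little further, to 0.6/0.275 = 2.2.

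**Step 5. What it could hide.** With a flat control arm, a linear fall *x* in the Myosuit arm is cancelled when (*u* − *x*/2) × *W* = *u* × (*W* − 1), so *x* = 2*u*/*W*. For *W* = 9 this is 0.13, 0.16 and 0.18; for *W* = 10 it is 0.12, 0.14 and 0.16.

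**Step 6. The other reading.** If *gained* means area minus T0 utility × time, each participant's value is 0.5 × (T5 − T0 utility) × *W*/52. With no change in utility this is 0 in both arms. With the same 0.05 rise in both arms it is 0.5 × 0.05 × 9/52 = 0.0043 against 0.5 × 0.05 × 8/52 = 0.0038. A difference of about 0.0005 remains, far smaller than in Step 3.

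**The case against.** The strongest reply is that the bias depends on which of two descriptions governs. The QALY section is headed as gain and speaks of *gained* QALYs, and the analysis section calls T0 the pre-intervention value, which could make it a reference to subtract. On that reading Step 6 applies and the artefact is zero for an unchanged utility. This stands in part: a reader might infer that the trial is certain to report a spurious QALY benefit, and the article does not support that. But the section that defines the analysis says *total* and describes no subtraction, so the biased reading is the one on the page. Even the gain reading leaves unequal accrual of any real change.

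Second, 12.5% is the top of the range. This stands. The 9 and 8 weeks are sums of phase lengths, not stated visit weeks; a shared lead-in lowers the percentage to 11.1% or 10.0%, and rescheduled training sessions will vary the actual intervals. The absolute excess and its direction do not change, though its size rests on an assumed utility.

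Third, the full protocol, which is not shown, may set a horizon. It may. But the point here is a stated rule applied to stated unequal windows, not a missing detail.

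Fourth, this is the last-listed objective, and the article specifies only differences in averages, with no test, cost-effectiveness ratio or decision threshold. This stands, and it limits the severity.

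**Conclusion.** The point holds with limits. As the analysis section is worded, the Myosuit arm is credited with about 10 to 12.5% more QALYs under no effect. At an assumed utility of 0.6 to 0.8 that is 0.0115 to 0.0154 QALYs, roughly 2.4 to 3.6 times an assumed true linear gain of 0.05 when the shared lead-in is at most one week.

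The conclusion rests on the stated phase lengths, on *total* meaning the unsubtracted area, and on each arm's own T0–T5 window being used. If *gained* means area minus T0 utility × time, the artefact vanishes for an unchanged utility, and only the unequal accrual of real changes is left.

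A reader might go further and see a flaw that undermines the trial. The documents do not support that: walking time, gait capacity and usability are unaffected, and no decision rule hangs on the QALY difference. It should be fixed before the analysis, as a matter for this secondary comparison only.

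**What to change.** In Statistical methods, Secondary outcomes:

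1. **Common horizon.** Compute QALYs over one fixed period for everyone. For example, divide each participant's area by their own T0–T5 time and multiply by 8/52 years, which equals the mean of T0 and T5 utility × 8/52. At a constant utility of 0.7 both arms then give 0.1077 and the difference is 0.
2. **Baseline adjustment.** Compare the arms with T0 utility as covariate, as is done for the gait outcomes. Without it, half of any chance T0 difference passes directly into the result, with about 17 participants per arm.
3. **One definition.** Reconcile *total* here with *gained* in the QALY section. Once steps 1 and 2 are in place, the choice no longer alters the arm estimate: the two versions differ by T0 utility × 8/52, a multiple of the covariate.

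The cost is a sentence or two of analysis wording, with no new visits or data. Relative to the total-area reading, the QALY difference becomes less favourable to the Myosuit. T5 will still fall a week later after the start in that arm; rescaling removes the effect of window length, not that difference in timing.
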